## Limitations

This study has some limitations. The survey that provided data on mediator variables included 187 of the 209 CCGs existing at the time of the study. However, this sample size is large enough for strong statistical power, and multiple imputation will be used to address issues on missingness. Furthermore, due to the limited data on practice-level interventions or strategies that might potentially mediate the effect of the QP on antibiotic prescribing, we will not be able to extensively investigate the mechanism of QP impact at the practice level. Nevertheless, extensive investigations will be conducted at CCG level where we have more data on potential mediators.

In 2013, the Primary Care Trusts in England, which were responsible for planning and commissioning healthcare services at the primary care level, were transformed to CCGs.^50^ As such, our investigations are restricted to the CCG era. This is important as the QP initiative is implemented and rewards paid out at CCG level.

We recognise that the causal interpretation of any effect from our mediation analysis rests on assumptions such as sequential ignorability and exchangeability. Causal inference from this analysis will be limited given that our data are observational with the absence of random assignment of cases to treatment and mediator levels, as well as the likelihood of unmeasured confounders. The rate of consultation for conditions where antibiotics might be prescribed is one of the unmeasured confounders in our study. This has not been accounted for in our analyses as these data are not available nationally at the practice level.

## Discussion

Although the QP intervention has been reported to have been effective in reducing antibiotic prescribing,^22^ there remain important gaps in the evidence base for this intervention, especially in relation to its mechanism of impact. This study will be the first to evaluate the mechanism of the impact of a financial incentive initiative involving CCGs to improve antibiotic prescribing in primary care practices in England. If our study identifies some key mediators, like other interventions implemented in similar time or in response to the QP initiative, that explain the indirect effect of the QP intervention on antibiotic prescribing, this will provide important evidence on the effectiveness of the implementation of a package of interventions on antibiotic prescribing. The investigation of multiple mediators in this study will also help to highlight the contributions of multiple factors in translating the effects of QP while unpacking the extent of the effect of specific mediators.

Evidence on the mechanism of impact of strategies like QP will be important in improving its uptake and sustainability while maximising its potential in reducing antibiotic prescribing in primary care settings.

Finally, financially incentivised strategies for clinical compliance have been criticised for their ability to result in unintended consequences.^51^ In the case of the QP initiative, unintended consequences like not prescribing antibiotics in cases where they are indicated are possible. However, some of the QP response strategies that we hypothesised as potential mediators (such as prescribers’ AMS education/training) have the ability to mitigate this unintended consequence. By comparing the prescribing rate before and after the QP initiative and identifying the strategies that explain its effect, we will generate evidence that will be important in considerations of the future of this intervention and revisions that may help reduce potential unintended consequences.

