The impact of interventions on specific outcomes is sometimes explained by a series of events. Potential mediators are important in assessing causal relationships like that between QP and antibiotic prescribing in primary care practices in England, where a potential mediator is a variable that hypothetically mediates the effect of QP on the outcome. The conceptual model shown in figure 1 demonstrates the hypothesised pathways for the impact of the QP initiative on antibiotic prescribing and subsequently AMR. The model is developed based on conceptual and empirical evidence from existing literature and the results of qualitative and survey studies conducted as initial stages of the broader STEP-UP (Improving the uptake and SusTainability of Effective interventions to promote Prudent antibiotic Use in Primary care)^25^ project that includes the current study. The conceptual model will be further validated through a stakeholder workshop with key antibiotic stewardship personnel, primary care prescribers and CCG representatives.

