**Figure 1 F1:**
[figure not shown]
Conceptual model. The direct effect is represented by the path between the QP initiative (predictor) and antibiotic prescribing rate (outcome). *Not directly observed within our data. AMS, antimicrobial stewardship; CCG, Clinical Commissioning Group; CMO, Chief Medical Officer; QP, Quality Premium; TARGET, Treat Antibiotics Responsibly, Guidance, Education, Tools.

Our conceptual model suggests that in addition to its direct impact, the QP initiative acts by stimulating and enhancing the adoption of existing strategies to reduce and optimise antibiotic prescribing. In investigating the potential pathways connecting QP to reductions in antibiotic prescribing, we will be examining the hypothesis that factors like the Chief Medical Officer’s (CMO) letter, Treat Antibiotics Responsibly, Guidance, Education, Tools (TARGET) toolkit, antibiotic auditing, benchmarking, local incentives at CCG level, prescribers and patients’ antimicrobial stewardship (AMS) education/training can transmit part of the influence of the QP initiative to antibiotic prescribing.

First implemented in September 2014, the CMO letter, which provided social norm feedback to primary care practitioners in England whose antibiotic prescribing rate was in the top 20%, reduced antibiotic prescribing by 3.3% in 6 months in a randomised trial.^26^ The criteria for selecting practices that received the letters in the subsequent years changed with the addition of measures like a change in antibiotic prescribing over time and whether practices have previously been sent CMO letter.

Another important mediator hypothesised in our conceptual model is AMS education/training of prescribers and patients. Educating and training prescribers on the importance of antibiotic stewardship and ways to promote prudence can help prescribers make better decisions on when an antibiotic is indicated and can also improve patients’ knowledge on the appropriate use of antibiotics. AMS interventions targeted at patients can improve their knowledge of when antibiotics are not needed and increase confidence and skills on how to self-care, which can result in reduced consultations for self-limiting illness and thus reduced antibiotic prescriptions.

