TARGET is a toolkit developed by the Public Health England (PHE), the Royal College of General Practitioners and other professional societies to promote prudent antibiotic use among prescribers and patients in primary care.^27^ The intervention comprises of multiple resources (patient information leaflets on infection management and antibiotic use, self-assessment checklist for prescribers, antibiotic audit toolkits, interactive workshop presentations, national antibiotic management guidance, training resources and resources for clinical and waiting areas) to provide clinicians and patients with the motivation and skills to use antibiotics prudently.^27^ A qualitative study evaluating prescribers’ attitude and perception about the TARGET toolkit reported that general practitioners described it as useful and important in improving their prescribing behaviours and the expectations of their patients.^28^ The use of resources like the TARGET antibiotics workshop has been shown to reduce antibiotic prescribing rate in a randomised controlled trial.^29^

We hypothesise that the implementation of the QP initiative informed the initiation or wider use of these strategies indicated in the conceptual model as mediators, which will subsequently influence antibiotic prescribing at primary care practices.

The implementation of the QP initiative in NHS England constitutes a natural experiment and offers an opportunity to investigate the preintervention and postintervention periods to understand the mechanism of impact of the QP intervention in reducing antibiotic prescribing rates in primary care practices.^30^ Given the ethical and practical constraints in manipulating exposure in such an intervention, a natural experimental design offers a practical approach to understand the overall effect and mechanism of interventions like QP that offers financial incentives for clinical compliance. The publication of the 2015/2016 QP Guidance^18^ constitutes the ‘intervention’, with periods before this as the ‘control’.

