### Variables

The predictor will be a binary variable indicating the implementation of the QP intervention. The intervention will include all periods after March 2015 when the 2015/2016 QP guidance in England was published, while the control will be periods prior to this. The primary outcome of interest is the rates of antibiotic prescribing at CCG level in England, which will be a continuous variable indicating the number of items (per STAR-PU) prescribed per month.

To account for differences in practice and CCG characteristics that can contribute to variance in antibiotic prescribing, we will be adjusting for the number of general practitioners in each practice (from the NHS Workforce data),^35^ the index of multiple deprivation (from the Department for Communities and Local Government),^36^ prevalence of comorbidities (asthma, chronic obstructive pulmonary disease, diabetes, cancer, chronic kidney disease (from the NHS Quality and Outcomes Framework database)),^37^ the prescribing rate of other non-antibiotic drugs (opioids and benzodiazepines) and seasonal influenza vaccination rate (from PHE).^38^

Mediator variables will be derived from the questionnaire data from a PHE survey,^39^ with 187 of the 209 AMS leads representing CCGs in England and data from other organisations that have evaluated the interventions treated as potential mediators in this study. In the PHE survey, participants were required to complete questionnaire items, which included their adoption of national and local strategies in their respective CCG to enable them to meet QP targets on antibiotic prescribing in primary care. The mediator variables will be binary or continuous variables, indicating the adoption of key interventions and intermediaries that are hypothesised to reflect in the integration of the QP guidance in improving antibiotic prescribing in primary care practices.

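### The Discussion counts interventions that only coincide with the Quality Premium as its mediators, and the before/after mediation contrast cannot tell them from strategies that it prompted

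*Protocol article*

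**What the plan says.** The Introduction gives the definition: "a potential mediator is a variable that hypothetically mediates the effect of QP on the outcome". After describing the conceptual model it states the causal link on which that definition depends: "We hypothesise that the implementation of the QP initiative informed the initiation or wider use of these strategies". Both require QP to act on the mediator.

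The Discussion, looking ahead to possible findings, refers to "key mediators, like other interventions implemented in similar time or in response to the QP initiative, that explain the indirect effect". The alternative in that phrase lets timing alone qualify an intervention.

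The Chief Medical Officer's (CMO) letter is one of the listed candidate mediators. On its timing: "First implemented in September 2014, the CMO letter, which provided social norm feedback to primary care practitioners in England". On its effect: it "reduced antibiotic prescribing by 3.3% in 6 months in a randomised trial". Recipients were first chosen as the highest-prescribing fifth, and later criteria changed with the "addition of measures like a change in antibiotic prescribing over time and whether practices have previously been sent CMO letter". QP is not named among the criteria.

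Under Variables, the exposure is binary: after March 2015 against before. Mediators come from a survey of antimicrobial stewardship leads, whose items concern strategies taken up to meet QP targets, and from "data from other organisations that have evaluated the interventions treated as potential mediators in this study". Under Statistical analysis, each mediation dataset sets the one financial year before QP against one later financial year. Candidates found to mediate when fitted singly go forward to the multiple-mediator model.

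**The concern.** A strategy that spread over the same years for other reasons is not on the path from QP to prescribing. It is a co-intervention that confounds a before/after comparison. If it is modelled as a mediator, its effect sits inside the QP total effect and is then presented as part of how QP worked. The study means to inform decisions on the future of the incentive, so crediting QP with the effect of an independent programme would bear directly on that use.

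The Discussion wording matters because nothing in the described analysis would correct it. The design treats QP-prompted and coincident uptake identically.

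**Working it through.** The protocol gives no figure for this point that could be reproduced. The check sets the texts side by side, writes out what the design estimates, and illustrates its scale.

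**1. The texts.** The Introduction requires that QP act on the strategy. The Discussion accepts that, or mere coincidence in time. The second set contains the first and adds interventions that QP did not cause. The two cannot both define the mediators of one indirect effect.

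**2. What the contrast estimates.** Let uptake of a strategy be p0 in the pre-QP year and p1 in the post-QP year, and let b be its effect on prescribing. Exposure is the year, so the exposure-to-mediator path is

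a = p1 − p0 = a(QP) + a(other).

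In the simple linear case the estimated indirect effect is a × b = a(QP) × b + a(other) × b. Only the first term belongs to QP. The second enters both the indirect and the total effect. With no concurrent control, the two parts of a cannot be separated from these data.

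**3. Whether planned steps intervene.**
- Screening on a single-mediator effect does not help: a coincident strategy that spreads and works will pass.
- The dummy implementation dates move the exposure by 1 to 3 months, which tests anticipation and lag.
- The listed covariates include no concurrent stewardship programme.
- The workshop is to validate the conceptual model, help order the mediators and identify which affect one another. Sorting candidates by whether QP prompted them is not among its stated tasks.
- The interrupted time series allows for the earlier trend, but for the total effect only.

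**4. Illustration of scale.** Inputs: b = 3.3%, the letter's trial effect in the Introduction; a(other) = 20 to 40 percentage points, an assumption with no basis in the document.
- 0.20 × 3.3% = 0.66%
- 0.40 × 3.3% = 1.32%

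For comparison, the 2015/16 target in the Introduction was a 1% reduction.

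**5. Illustration of the screen.** A simulation of 1,000 runs took 209 CCGs (Clinical Commissioning Groups) per period, a mediator effect of −3.3%, a residual SD of 5% (assumed) and no QP effect of any kind. It used the product of coefficients with a Sobel test.

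| Uptake, non-QP causes only | Mean estimated QP indirect effect | Significant runs |
|---|---|---|
| 20% to 40% | −0.66% | 99.1% |
| 20% to 60% | −1.32% | 100% |
| 20% to 80% | −1.99% | 100% |

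The true indirect effect was zero throughout. This is not the planned unified model, and the inputs are assumed. It shows the mechanism, not that this study's mediators behave so.

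**The case against.** The strongest reply is that the Discussion sentence is conditional and sets no rule. A reader might infer that the protocol selects mediators on timing. The documents do not support that: candidates come from a conceptual model built on literature, qualitative and survey work, and no Methods text admits a variable because of when it ran. This stands.

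Second, the conceptual model has QP strengthening strategies that already existed. A strategy that began earlier, the letter included, can therefore still be a partial mediator. This stands too, and it argues against simply reclassifying such strategies.

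Third, the survey items are framed around meeting QP targets, so it would be wrong to infer that every mediator is affected. What remains is the letter and the data from other organisations, for which the article states no tie to QP. The article is condensed, and a fuller document might supply one.

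Fourth, a reader might multiply the letter's effect by the fifth of practices first targeted, 0.20 × 3.3% = 0.66%, and call that the bias. This does not follow. The letter began in September 2014; if the financial year runs from April to March, it was already in use for 7 of the 12 control-year months. Only a later change in its reach or effect would distort the contrast.

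Fifth, Limitations concedes reliance on sequential ignorability and exchangeability, and likely unmeasured confounders. That discloses the problem only in general terms: the one confounder named is consultation rate, and concurrent interventions are not mentioned.

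**Conclusion.** The concern holds in limited form. The Discussion describes as mediators interventions that need only coincide with QP, which conflicts with the Introduction. The year-against-year exposure cannot repair this, because any change in uptake is read as the QP-to-mediator path. The exposure to error lies with strategies that the survey wording does not tie to QP: the CMO letter and mediators taken from other organisations' data. For these, part or all of a non-QP effect can be reported as an indirect effect of QP.

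The direction follows from the design: a rise in uptake that QP did not cause, in a strategy that lowers prescribing, inflates the apparent QP effect. The size cannot be derived from the document. The 0.66% to 1.32% rests on an assumed rise and on a six-month trial effect of one strategy, so it indicates order of magnitude only.

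**What to change.** 1. In the Discussion sentence, strike the alternative that admits interventions on timing, leaving only those taken up in response to QP.
2. At the stakeholder workshop already planned, and before analysis, classify each candidate under Variables as QP-prompted or not clearly QP-prompted. A survey item recording adoption to meet QP targets, or dated evidence that QP prompted the uptake, would support the first class.
3. For candidates not clearly QP-prompted, do not default to covariate adjustment. Report the QP total and indirect effects twice, once with the strategy as a mediator and once as a co-intervention covariate, and present the two results as a range.
4. In Limitations, name concurrent interventions as a confounder of the before/after contrast.

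The cost is wording, one workshop item and one extra model run. The QP effect may have to be reported as a wider range. Where QP partly caused the uptake, the covariate version conditions on a consequence of QP and understates its effect, so it should be read as one end of the range and not as the corrected answer.

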### Patient and public involvement

This study will use secondary data mostly from routine collection system and will not directly involve patients or the public. The dissemination of the results will include communication channels and public engagement events that will involve primary care practitioners and CCG representatives.

### Ethics and dissemination

Prescribing data from NHS BSA and NHS Digital are generated from routinely collected prescribing data on items that have been dispensed in primary care practices in England. The survey that produced the data on mediator variables was registered with the PHE Research Support and Governance Office (RSGO) and approved by PHE Research Ethics and Governance Group (REGG) and Health Research Association (HRA).

Multiple channels will be used in disseminating the findings from this study to academic and non-academic audiences, which will include an engagement workshop with our stakeholder network, presentations in scientific conferences, publication in peer-reviewed journals and press conference coinciding with paper publications.
